## Abstract

**Background::**

Bipolar disorder (BD) is a chronic and disabling psychiatric disorder. The treatment of BD still remains a significant clinical challenge due to the complex nature of the disease. Nutraceutical therapy as adjunctive role is a promising therapy for BD. Sulforaphane (SFN), a broccoli extract, was reported to be effective for emotional problems and cognitive impairment. However, clinical research of SFN in the treatment of BD was rare. Therefore, this study is designed to evaluate the adjuvant role of SFN in the treatment of BD.

**Methods::**

This is a randomized, double-blinded, placebo-controlled, parallel-group clinical trial. A total of 100 patients who meet inclusion criteria will be assigned to receive quetiapine plus SFN or quetiapine plus placebo in a 1:1 ratio. The total duration of the study will be 12 weeks including 5 follow ups. The primary outcome is in the Montgomery–Asberg depression rating scale. The secondary outcomes are the quick inventory of depressive symptomatology—self report, Hamilton anxiety rating scale, young mania rating scale, cognitive function, inflammatory factors, and intestinal flora. Any adverse events will be recorded throughout the trial.

**Discussion::**

This trial will provide evidences to evaluate the efficacy and safety of SFN combined with quetiapine in the treatment of BD patients, as well as the adjuvant role of SFN in combination.

**Trial registration::**

This study protocol was registered at the Chinese clinical trial registry (ChiCTR2000028706).

## Introduction

1

Bipolar disorder (BD) is a common psychiatric disorder characterized by manic and depressive episodes, leading cause of global disability. Bipolar depressive disorder is associated with longer illness duration and poorer response to treatment than mania, impairing quality of life, social relationship, and occupational performance.^[1,2]^ The treatment of bipolar depression is mainly emotional stabilizer, second generation antipsychotics. Clinical recommendation supported atypical antipsychotic drugs as quetiapine, lurasidone for treatment of acute bipolar depression.^[3,4]^ Adverse events (AEs) at recommended doses of the psychoactive agents including akathisia, somnolence, sedation, and metabolic syndrome are associated with treatment compliance and poor treatment outcomes for patient with BD.^[3,5–7]^ Hence, for managing BD, more effective and safer interventions are urgently needed.

There is now significant evidence implicating genetic susceptibility, neurotransmitter imbalance, inflammatory oxidative stress, neurotrophic factor signal transduction deficiency, and neuroendocrine abnormality in the pathophysiology of BD.^[8–13]^ Activated immunity and elevated biomarkers for inflammation were found in patients with BD.^[14,15]^ In addition, compared with the healthy controls, there were inflammatory changes in the prefrontal cortex of BD patients in post-mortem studies, mainly manifested by decreased anti-inflammatory factor level and increased inflammatory factor level.^[16]^ The widely accepted hypothesis of inflammation, oxidative stress, and abnormal immune regulation are therapeutic targets for bipolar depression.

Recently, there has been an increasing interest in the use of plant-derived natural products as complementary treatments with less toxic and fewer side effects. Sulforaphane (1-isothiocyanate-4-methylsulfonyl-butane, SFN), a common antioxidant derived from cruciferous vegetables has been used widely in cancer treatment.^[17]^ It plays a role in the antioxidant and prooxidant activities, canonically acting through the inhibition of inflammatory cytokine production and down regulation of nuclear factor-kappa B activity which ultimately affect the occurrence and progression of mental disorders.^[18–21]^ At present, SFN has been used to treat mental disorder in the clinical studies, such as autism, and has achieved positive results.^[22,23]^ Shiina et al reported that SFN improved cognitive function in patients with schizophrenia.^[24]^ What's more, SFN was proving owning a certain inhibitory effect on depression-like behavior associated with inflammation-induced depression in mice.^[25–27]^ However, the adjuvant effect of SFN in the treatment of patients with BD has never been studied and remains unknown.

In summary, SFN can influence the oxidative stress–inflammation pathways, resulting in a positive effect on cognitive and emotional development. This study aims to observe the adjuvant effects or improvement effects and safety of SFN in the quetiapine for bipolar depressive disorder, and explore the mechanisms by detecting changes in inflammatory factors and intestinal flora before and after treatment.

## Methods

2

### Study design and ethics approval

2.1

This is a randomized, double-blinded, placebo-controlled, parallel-group clinical trial. This protocol was approved by the Research Ethics Committee of the First Affiliated Hospital, College of Medicine, Zhejiang University (December 24th, 2019). The trial which is registered at the Chinese Clinical Registry (ChiCTR2000028706) will be conducted in the First Affiliated Hospital, College of Medicine, Zhejiang University in China. The clinic trial was supported by the grant of the National Natural Science Foundation of China (81971271). Figure 1 depicts a flow chart of the study. Patients enrolled in this study will randomly be assigned into 2 groups (with a 1:1 allocation ratio). Clinical manifestations and assessment scales, neurocognitive functions, and some of the blood biochemical tests will be checked before treatments started (baseline) and will be reexamined on week 2, 4, 8, 12 weeks of treatment to assess the effectiveness and safety. Meanwhile, inflammatory cytokines and intestinal flora were monitored during follow-up. Researchers will record and deal with the any adverse reactions and assess whether they can continue the experiment to protect the participants’ interests during the study. Specific schedules are summarized in Table 1.

**Figure 1 F1:**
[figure not shown]
Flow chart of the study.

**Table 1 T1:**
[figure not shown]
Schedule of the enrollment, intervention, and assessments in the process.

### Study population

2.2

Participants who meet the eligibility criteria and sign informed consent will be enrolled in the study. Inclusion criteria for enrollment are described as follows:

(1)males or females aged 16 to 65 years old;(2)agree to participate in the research and sign the informed consent form;(3)the subjects biological parents are Han;(4)diagnosed with bipolar depressive disorder according to the fourth Edition of Diagnostic and Statistical Manual of Mental Disorders diagnostic criteria;(5)score more than or equal to 17 points on the Hamilton depression scale at screening and baseline period;(6)score less than or equal to 5 points on the young mania rating scale (YMRS) at screening and baseline period;(7)no taking any drug treatment or no receiving antidepressant treatment in the last 1 month;(8)take drugs by oneself during the study period, or have a regular helper to help with the medication.

Exclusion criteria are described as follows:

(1)diagnosed with other spectrum disorders according to the fourth Edition of Diagnostic and Statistical Manual of Mental Disorders diagnostic criteria;(2)mental disorder caused by substance abuse, or serious physical diseases;(3)received antibiotics within 1 month before enrollment due to respiratory tract, urinary tract, the digestive system infection;(4)subjects with a history of attempted suicide, or currently at high suicide risk, or with suicide behavior/attempt, or scoring more than or equal to 3 points on the 10th clause of Montgomery Asberg Depression Rating Scale (MADRS);(5)unwilling to take the medicine;(6)known pregnancy, lactation, or pregnant planning;(7)the subjects with contraindications of quetiapine or have used quetiapine but have poor efficacy;(8)allergic to broccoli;(9)received electroconvulsive therapy within 1 month.

Suspension criteria are as follows:

(1)subjects with serious adverse drug reactions;(2)exchange drugs or receive other treatment due to unstable condition;(3)refuse to continue participating in the study;(4)lose track in follow-up;(5)other factors cause the interview to stop.

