### Outcomes

2.5

Primary outcome is the change in the MADRS scores at baseline compared to each treatment time point. MADRS is a clinician-administered rating scale and widely used to assess the depression severity of patient with BD. The response was defined as at least a 50% reduction when compared to baseline in the scores.

While secondary outcomes include the scores of the quick inventory of depressive symptomatology-self report, Hamilton anxiety rating scale, and YMRS scores are used to elevate the broader affective symptoms. Besides, cognitive function which tested by THINC-integrated tool, inflammatory factors (interleukin-2, interleukin-4, interleukin-6, interleukin-10, interleukin-17A, tumor necrosis factor and interferon-γ) and intestinal flora are used to investigate the underlying biological factors.

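### Exclusion criterion 3 bars recent antibiotics for only three infection sites, so some baseline flora and cytokine samples may follow an antibiotic course (minor)

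*Protocol article*

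**What the plan says.** In the Protocol article, section 2.2 (Study population), exclusion criterion 3 applies to patients who "received antibiotics within 1 month before enrollment due to respiratory tract, urinary tract, the digestive system infection". The rule has two conditions: a window of one month before enrolment, and an infection at one of three named sites.

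The only other pre-enrolment drug restriction that could reach an antibiotic is inclusion criterion 7 in the same section: "no taking any drug treatment or no receiving antidepressant treatment in the last 1 month".

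The samples at issue serve the mechanism objective. The Introduction (section 1) aims to "explore the mechanisms by detecting changes in inflammatory factors and intestinal flora before and after treatment". Section 2.5 (Outcomes) lists seven cytokines and intestinal flora among the secondary outcomes and says that these and "intestinal flora are used to investigate the underlying biological factors". Section 2.8 (Statistical analysis) plans between-group tests (t, chi-squared or Wilcoxon Mann–Whitney) and a paired t test within each group.

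**The concern.** The article does not say why exclusion criterion 3 exists. Two purposes are plausible, and the site limit fits neither.

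- **To protect the flora outcome.** A systemic antibiotic can act on the gut whatever infection it was prescribed for, so the indication is the wrong thing to restrict.
- **To keep recent infection out of the cytokine data.** Infections at other sites are inflammatory too.

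A patient who finished an antibiotic for a dental or skin infection shortly before enrolment is therefore not clearly excluded. That patient's baseline sample may still be recovering, and the later return towards the usual state is then counted as change from baseline. At stake are the interpretability of the within-group before/after results and some precision in the between-group flora and cytokine comparisons.

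**Working it through.** The plan gives no figure to reproduce on this point. The check is a reading of the criteria, followed by an illustration of size.

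**Step 1. Does exclusion criterion 3 cover other indications?** Read as written, no. Respiratory, urinary and digestive infections are named, and nothing marks them as examples.

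**Step 2. Does inclusion criterion 7 close the gap?** Let A be no drug treatment in the last month and B be no antidepressant in the last month. Anyone who satisfies A also satisfies B.

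| Reading of inclusion 7 | What it requires | Antibiotic for a skin infection last week |
|---|---|---|
| Either A or B suffices | A or B = B: no antidepressant | Not barred |
| Both A and B are required | A and B = A: no drug at all | Barred, and exclusion 3 becomes redundant |
| Drug treatment means psychiatric drugs | Silent on antibiotics | Not barred |

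Only the second reading closes the gap, and it leaves exclusion criterion 3 with nothing to do. The two criteria need reconciling on any reading.

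**Step 3. Which comparisons are exposed?** Let q be the proportion of patients with an affected baseline sample and δ the average shift in a flora or cytokine measure in those samples.

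- *Within group.* The mean change from baseline moves by q × δ in size. For q = 5%, 10% and 20% this is 0.05δ, 0.10δ and 0.20δ. Randomisation does not remove it.
- *Between groups.* The expected shift is (q − q) × δ = 0. What remains is chance imbalance: a difference of d between the arms' proportions moves the between-group contrast by d × δ, so a 10-point imbalance carries over one tenth of δ.

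**Step 4. How likely is chance imbalance?** Inputs: 50 per arm (section 2.7, Sample size) and q = 5%, 10% or 20% in both arms (assumed). The standard deviation of the difference in proportions is √(2q(1 − q)/50). The tail probabilities come from the exact distribution of the difference between two Binomial(50, q) counts; 10 points is 5 patients and 20 points is 10 patients.

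| Assumed q | SD of difference | Chance of ≥10 points | Chance of ≥20 points |
|---|---|---|---|
| 5% | √(0.095/50) = 4.4 points | about 4% | below 0.1% |
| 10% | √(0.18/50) = 6.0 points | about 13% | about 0.2% |
| 20% | √(0.32/50) = 8.0 points | about 26% | about 1.7% |

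Moderate imbalance is possible at the higher assumed rates; large imbalance is rare. The table counts any exposure at rate q. The share admitted through the gap in exclusion criterion 3 is unknown and could be lower than any of these values.

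**The case against.** The strongest reply is that little depends on this. The article states "This is a randomized, double-blinded, placebo-controlled, parallel-group clinical trial", so antibiotic exposure should balance on average, and the between-group test already allows for chance imbalance. Flora and cytokines are secondary outcomes, and the Discussion calls the trial exploratory and asks for cautious interpretation. Both arms also start quetiapine (section 2.4), so a within-group change could not be credited to SFN even with clean baselines. All of this stands. It limits the severity but does not justify the site restriction, and the within-group tests are still planned and would still be distorted.

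A reader might go further and infer that the flora results could reflect antibiotics rather than SFN. As a claim about the randomised comparison, the documents do not support it: that would need exposure to differ systematically between arms, and nothing in the design suggests that it would.

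A reader might also infer that antibiotics taken during the 12 weeks are uncontrolled, because "inflammatory cytokines and intestinal flora were monitored during follow-up" while the nearest suspension criterion covers only patients who "exchange drugs or receive other treatment due to unstable condition". That cannot be sustained either. Rules on concomitant medication are commonly left to the full protocol, and the contents of Table 1 are not available here. Section 2.6 (Safety assessment) has adverse events assessed at each visit, with onset and end dates and the action taken entered on the form. An intercurrent infection and its treatment could be captured there, although antibiotic start and stop dates are not guaranteed.

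Finally, the sponsor may have meant the three sites as examples, or may read inclusion criterion 7 strictly. Either would close the gap in practice, but the text says neither.

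**Conclusion.** The point holds as a minor defect in a stated eligibility rule. Exclusion criterion 3 leaves out recent systemic antibiotics given for infections other than the three named, and inclusion criterion 7 does not reliably cover them. The consequence is noise and possible chance imbalance in the secondary flora and cytokine comparisons, and possible distortion of the within-group before/after tests. No systematic between-arm bias is expected, and the MADRS primary outcome is not affected.

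The size cannot be fixed from the documents. The 5% to 20% range is an assumption, the flora sampling visits are not visible, and nothing shows what share of antibiotic courses falls outside the three sites. It would therefore be wrong to say that the rule misses most of the exposure, or to give a count of affected patients as a finding. That the criterion exists to protect the flora outcome is a plausible inference, not something the article states.

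**What to change.** Delete the clause in exclusion criterion 3 that lists infection sites, so that it covers any systemic antibiotic in the month before enrolment whatever the indication. Reword inclusion criterion 7 so that it is clear whether one or both of its conditions must be met and which drugs it covers, and check that the two criteria agree.

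Optionally, use the treatment measures already recorded on the adverse event form (section 2.6) for one pre-specified sensitivity analysis of flora and cytokines. It would set aside samples taken within one month after an on-study antibiotic course and be reported beside the analysis of all samples. Patients stay in the trial and in all clinical analyses.

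The cost is a change to two eligibility criteria, slightly more screen failures and, if the option is taken, slightly fewer samples in that sensitivity analysis.

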### Randomization and blinding

2.3

The enrolled participates will be randomly assigned a random number sequence which generated by SAS ver.9.0 for Microsoft Windows (SAS InstituteInc, Cary, NC) in a 1:1 ratio. A sealed envelope, independently managed by a third researcher was used to allocation concealment. The researcher will not take part in follow-up and assessment. Neither assessors nor subjects will know the assigned group and the intervening measure until the study is terminated.

### Groups and interventions

2.4

In this study, enrolled bipolar depressed patients are randomly assigned into 2 groups: SFN group and placebo group and will undergo 12-week quetiapine concomitantly. The initial treatment dose of quetiapine in the 2 groups are 50 mg daily, and will be added to 300 mg daily within 2 weeks. The patients in SFN group will receive 1 tablet of Avmacol Extra Strength (480 mg) daily swallowed with warm water (no more than 40 degrees) after breakfast or chewed at the same meal, and placebo group will receive a placebo in the same way. Avmacol Extra Strength contains Proprietary Sulforaphane Glucosinolate (Glucoraphanin) & Myrosinase Blend 490 mg including Broccoli Seed & Sprout Extract (containing more than 30 mg of glucoraphanin). The placebo matches Avmacol Extra Strength with size, shape, taste, and package without any active ingredient. Both of them used in this study are produced by the Nutramax Laboratories Consumer Care (Lancaster, SC, USA).

### Outcomes

2.5

Primary outcome is the change in the MADRS scores at baseline compared to each treatment time point. MADRS is a clinician-administered rating scale and widely used to assess the depression severity of patient with BD. The response was defined as at least a 50% reduction when compared to baseline in the scores.

While secondary outcomes include the scores of the quick inventory of depressive symptomatology-self report, Hamilton anxiety rating scale, and YMRS scores are used to elevate the broader affective symptoms. Besides, cognitive function which tested by THINC-integrated tool, inflammatory factors (interleukin-2, interleukin-4, interleukin-6, interleukin-10, interleukin-17A, tumor necrosis factor and interferon-γ) and intestinal flora are used to investigate the underlying biological factors.

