### Sample size

2.7

It was absent of direct evidences to support t our hypothesis, consequently, estimating the sample size is difficult. At an 8-week study, the response rate of quetiapine in BD patients was 58.9%, and the remission rate was 42.1%.^[28]^ Combination therapy has been shown to be more effective. We estimated the effective rate of SFN combined with quetiapine in the treatment of bipolar depressive disorder to be about 70%. The sample size with 80% power at a significance level of 0.05 was calculated in this study. Anticipating a 10% dropout rate, a total of 100 patients, with 50 patients in each group, will be needed.

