### Statistical analysis

2.8

All statistical analyses will be performed using SPSS 19.0 software (IBM, Armonk, NY) in a blinded manner. Outcomes will be analyzed on the basis of intention-to-treat principle. Missing values will be handled by the practical guide described by Jakobsen et al. The comparison of primary outcomes and secondary outcomes between 2 groups will be performed by *t* test for continuous variables and *χ*^2^ test for categorical variables, or with Wilcoxon Mann–Whitney test. The paired *t* test will be used for analysis in each group. *P* < .05 will be considered significant

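### The primary outcome is MADRS change at each of four visits, with no primary visit or success rule; if any visit may count, the false-positive chance is about 9% to 18.5%, not 5%

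*Protocol article*

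**What the plan says.** Four sections of the protocol article bear on this.

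- **Section 2.5 (Outcomes):** "Primary outcome is the change in the MADRS scores at baseline compared to each treatment time point". The same paragraph defines response as a reduction of at least 50% from baseline, without saying whether response is itself a primary outcome.
- **Section 2.1 (Study design):** clinical scales and other measures are taken at baseline and "will be reexamined on week 2, 4, 8, 12 weeks of treatment to assess the effectiveness and safety". That makes four post-baseline time points.
- **Section 2.8 (Statistical analysis):** "The comparison of primary outcomes and secondary outcomes between 2 groups will be performed by *t* test for continuous variables", with a chi-square or Wilcoxon Mann–Whitney test as the alternatives. One threshold, P below .05, covers everything. No visit is singled out and no joint test across visits is named.
- **Section 2.7 (Sample size):** "The sample size with 80% power at a significance level of 0.05 was calculated in this study". Its control figure is a rate, not a mean change: "At an 8-week study, the response rate of quetiapine in BD patients was 58.9%, and the remission rate was 42.1" percent. That source ran for 8 weeks and treatment here lasts 12, so this section does not point to a primary visit either.

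The limitations paragraph of the Discussion calls the trial exploratory and asks for cautious interpretation.

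**The concern.** A primary outcome should lead to one answer. Here the text leads to four between-arm comparisons of the same scale, each judged at the full 5% level, and does not say how they combine. Success could mean significance at week 12, at any visit, at most visits or at all of them. These rules have very different error rates, and nothing in the article stops the choice from being made after the results are known.

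At stake is the 5% error level that the sample size section assumes. A difference seen only at week 2 or week 4 could be reported as meeting the primary outcome of a 12-week trial.

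**Working it through.** **The plan's own figure.** The article gives no error rate for the set of visits. Its only figure is the 0.05 level in sections 2.7 and 2.8. One test at one pre-specified visit reproduces it: the false-positive chance is 5% by construction.

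**Inputs from the article**
- Post-baseline visits: k = 4 (weeks 2, 4, 8, 12; section 2.1). The abstract counts five follow-ups; I use the four that the Methods name.
- Level per test: 0.05 (section 2.8). The number of sides is not stated; I take two-sided, so the critical value is c = 1.96.
- Planned size: 50 per arm (section 2.7).

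**Inputs that I assume**
- Success means P below .05 at one or more visits.
- The between-visit correlation ρ of the test statistics is not in the article, so I show a range.

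**Step 1, upper limit with independent visits.** 1 − (1 − 0.05)^4 = 1 − 0.8145 = 0.1855, or 18.5%.

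**Step 2, equal correlation between all visits.** With φ and Φ the standard normal density and distribution function,

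P(any |Z| > c) = 1 − ∫ φ(u) · [Φ((c − √ρ·u)/√(1−ρ)) − Φ((−c − √ρ·u)/√(1−ρ))]^4 du.

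**Step 3, correlation that falls with distance between visits.** First-order autoregressive by visit order, 1,000,000 simulated null draws per value.

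| ρ | Equal correlation | Autoregressive |
|---|---|---|
| 0.3 | 17.4% | not run |
| 0.5 | 15.6% | 16.6% |
| 0.7 | 13.0% | 14.3% |
| 0.8 | 11.4% | 12.7% |
| 0.9 | 9.4% | 10.4% |

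Across the two structures, correlations of 0.8 to 0.5 give 11.4% to 16.6%. The whole range, from 0.9 to independence, is 9.4% to 18.5%.

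**Step 4, check with actual t tests.** Simulated data with 50 per arm and equal correlation give 15.8% at ρ = 0.5 and 13.0% at ρ = 0.7, in line with Step 2.

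**Step 5, false positives in favour of sulforaphane only.** The figures above count errors in either direction. Counting only those that favour the add-on, with equal correlation, gives 8.7% at ρ = 0.3, 7.8% at 0.5, 6.5% at 0.7 and 5.7% at 0.8, against a nominal 2.5%.

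**Step 6, the opposite rule.** If all four visits had to be significant, the false-positive chance could not exceed that of any single visit, so at most 5%. The inflation therefore depends on the any-visit reading.

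**Step 7, after a correction.** One named visit gives 5%. Keeping four visits at 0.05/4 = 0.0125 each gives 4.9% if independent, 4.3% at ρ = 0.5 and 3.2% at ρ = 0.8 (equal correlation). Holm starts at the same 0.0125, so it has the same error when there is no effect at any visit.

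**The case against.** The strongest reply is that the article never says one significant visit is enough. Section 2.5 may simply list when MADRS change is measured, and a rule that all visits must be significant would not inflate the error at all. This stands, and it is why the percentages are conditional. It does not remove the defect, because no other rule is stated and the visits have equal primary status.

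A second reply is that an article condenses the full protocol, and that multiplicity rules usually sit in an analysis plan, which is not shown. That is fair, and the lack of an adjustment formula is not the point here. The definition of the primary outcome at every visit is the article's own text; an analysis plan that picked one visit would be changing it.

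Third, the authors call the trial exploratory. This lowers the severity. It does not alter the stated primary outcome, the threshold or the 80% power claim.

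A reader might also infer three stronger points that the article does not support:

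- **Eight primary tests, counting response at each visit.** Response is defined in the primary paragraph and the sample size uses a response rate, so its status is unclear. The article does not call it primary or say that it is tested at each visit.
- **Week 2 is invalid because quetiapine is still being raised then.** Section 2.4 has the dose raised over the first 2 weeks in both arms alike, so this creates no difference between the arms and has no bearing on type I error.
- **A positive trial could not be interpreted.** Visit-by-visit estimates from a randomised, blinded comparison remain informative. What is lost is the single claim at 5%.

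**Conclusion.** The point holds in conditional form. The article fixes four primary comparisons at P below .05 each and does not say which visit, or which combination, decides the result. If any one visit suffices, the two-sided false-positive chance is about 9% at an assumed between-visit correlation of 0.9, 11–17% at 0.8 to 0.5, and 18.5% at most, instead of 5%. At every correlation tried up to 0.9 it is close to double the nominal level or more.

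It would be wrong to state 11–17% as the trial's actual error rate: the correlations and the any-visit rule are both assumptions. The part that needs no assumption is that the success rule is undefined and could be chosen after the data are seen. The exploratory label tempers this, but the matter should be settled before unblinding.

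**What to change.** **Section 2.5:** name one primary endpoint, the between-arm difference in MADRS change from baseline to week 12, which is the planned end of treatment. List MADRS change at weeks 2, 4 and 8 and the response rate as secondary.

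**Section 2.8:** state that the primary endpoint is tested once at two-sided 0.05, and that the secondary visits and the response rate are reported as estimates with 95% confidence intervals. If all four visits must stay primary, use one joint test across visits or a Holm adjustment, and say which.

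**Section 2.7:** restate the sample size for the chosen endpoint, or say that 100 patients was not derived for it. The present basis is a response rate of 58.9% against an effective rate of about 70%, which does not carry over to a mean change. For orientation, 10% dropout leaves 50 × 0.9 = 45 per arm. A single two-sided t test then has 80% power for a standardised difference of (1.960 + 0.842) × √(2/45) = 0.59, or (1.960 + 0.842) × √(2/50) = 0.56 with no dropout.

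**Cost:** short edits to 2.5 and 2.8 and a rewrite of 2.7, with no change to the visit schedule. An isolated early difference can no longer be claimed as the primary result. Under Holm, the smallest of the four P values must fall below 0.0125 before any visit can be claimed, which costs power compared with a single test at 0.05.
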